### Intervention

2.5

The intervention has been designed by Healthily, a nurse led organization that provides a range of health resources for consumers and clinicians focused on building patient knowledge and capacity for self‐help. GoShare Healthcare is Healthily's flagship product and a customized content distribution platform for health professionals to share up‐to‐date, accurate and engaging healthcare resources tailored to the needs of individual patients. An extensive process of consultation and content development is undertaken with clinician and patient involvement to ensure that materials are appropriate, informative and reliable. The cardiac surgery platform contains a patient narrative library with a series of videos describing patient and carer experiences, in addition to animations and links to reputable on‐line resources. Evidence indicates patient narratives have a positive impact on patient education because the information they provide is vivid, engaging, relatable and understandable (Mazor et al., 2007; Winterbottom et al., 2008). When contrasted to written or factual education and communication strategies, narratives are a useful mechanism for encouraging patients to participate in shared decision‐making (Elwyn et al., 2006; Shaffer & Zikmund‐Fisher, 2013). Participants who feature in these videos are positive role models who share their experiences of the day‐to‐day challenges and strategies they use to manage their journey as a patient. The video series is based on current evidence and is designed to improve patient self‐efficacy and self‐management behaviours, and to empower people to play a more active role in their healthcare. Go Share has been developed to support integrated person‐centred care, health literacy and sharing health information. Customized care bundles can be sent to patients via email or SMS on an ad hoc basis or automatically delivered as a digital program at selected times. The platform is currently viewed on over 18,000 screens in over 80 hospitals for specific bundles, not including the cardiac surgery bundle.

The GoShare cardiac surgery bundles have patient narrative videos focused on receiving a diagnosis that requires surgical intervention and preparing for heart surgery, intermediate recovery after heart surgery and ongoing recovery after heart surgery. The videos are delivered by a mixture of male and female patients representing young to older adults. The patients in the videos do not discuss specifics of surgery or medical management, the focus is on strategies for self‐help and self‐efficacy in managing the cardiac surgical experience. The information sheets in the bundles link to resources such as those provided by the Australian Centre for Heart Health and the National Heart Foundation. In the bundle homepage there is an option for patients to provide feedback. To date the cardiac surgery bundle, whilst available for use, has not been tested for effect. Scheduled messaging for the mHealth intervention, as per patient preference via email or SMS, will take place at the time of randomization. The preoperative intervention bundle link will be sent once randomized. On the day of discharge from hospital after surgery, liaison nurses will contact RA‐1 to confirm discharge and trigger distribution of a link to the postoperative immediate recovery bundle in 7 days of discharge. The intermediate recovery bundle link will be sent in 30 days of the day of surgery.

### Outcome measures

2.6

This prospective multisite pilot study has been designed to test the effect of the cardiac surgery bundle on recovery as measured by representation and readmission rates in the intermediate and ongoing phases of rehabilitation from heart surgery. When readmission rates have been explored, a positive linear relationship with time after surgery is evident (Slamowicz et al., 2008). The primary outcome measures for this trial are representation and readmission in 30, 60, 90 days and at 12 months post surgery (reported separately). Readmission is a proxy for poor patient recovery and rates at 30 days are approximately 14% for isolated CABGS, incrementally increasing for valve, and CABGS with valve, respectively in Australian (Leppin et al., 2014) and international settings (Sun et al., 2008). Recent research emphasis the need to distinguish between representation and readmission that in combination occur in almost 27% of patients (Fox et al., 2013). Secondary outcomes include quality of life as measured by the short form EuroQol (EQ5D‐5L) (Brooks, 1996), and knowledge, skill and confidence for self‐management using the patient activation measure (PAM) (Hibbard et al., 2005). These measures will be assessed at baseline following enrolment and each time the primary outcome is assessed.

Testing in the pilot phase will enable sample size calculation based on the rate of 30‐day readmission to determine adequate power necessary for an ongoing prospective trial. Power analysis will be based on the assumption that readmission rates will be lowest at 30 days. Ongoing interim analyses will be undertaken to assess intervention effect on representation rate that is poorly reported, particularly in the Australian context. To be 95% confident that the readmission rate is in 10%, assuming 15% of the population will be readmitted, a total sample size of 49 patients is required. Loss to follow up, as indicated by 30‐day outcomes captured in the Australian and New Zealand Cardiac and Thoracic Surgeons (ANZSCTS) Database Registry, is approximately 4% annually. Each site performs an average of 10–15 cases per week. The aim is to recruit 20 patients from each site to a total of 60 patients, allowing for loss to follow up, prior to interim analyses in this pilot study. If two patients per week from each site can be recruited the trial should take approximately 10–12 weeks.

RA‐1 will maintain an electronic randomization schedule, and using a computer‐generated permuted block randomization schedule, randomize the patient to intervention or control. The enrolment, randomization and follow‐up schedules will be housed in separate sheets in REDCap to ensure liaison nurses and RA‐2 are blinded to allocation. It is not possible to blind patients to the intervention, and they may disclose allocation to RA‐2. Data analyses will be complete by an investigator not involved in recruitment, allocation or outcome measurement.

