**Methods:**

Adult patients scheduled to undergo elective cardiac surgery (coronary artery bypass grafting, valve surgery, or a combination of bypass grafting and valve surgery or aortic surgery) will be recruited from three metropolitan tertiary teaching hospitals. Patients allocated to the control group with receive usual care that is comprised of in‐patient discharge education and local paper‐based written discharge materials. Patients in the intervention group will be provided access to tailored ‘GoShare’ mHealth bundles preoperatively, in a week of hospital discharge and 30 days after surgery. The mHealth bundles are comprised of patient narrative videos, animations and links to reputable resources. Bundles can be accessed via a smartphone, tablet or computer. Bundles are evidence‐based and designed to improve patient self‐efficacy and self‐management behaviours, and to empower people to have a more active role in their healthcare. Computer‐generated permuted block randomization with an allocation ratio of 1:1 will be generated for each site. At the time of consent, and 30, 60 and 90 days after surgery quality of life and level of patient activation will be measured. In addition, rates of representation and readmission to hospital will be tracked and verified via data linkage 1 year after the date of surgery.

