### Limitations

3.1

This pilot study is to our knowledge, the first to test the effect of an mHealth intervention on recovery after adult cardiac surgery. The feasibility of the intervention has not previously been tested in a cardiac surgical context. In a pilot study for weight management in young adults the GoShare platform was shown to be a feasible and acceptable mechanism to augment self‐efficacy and self‐management but no more effective than usual care (Hebden et al., 2014). However, there was variability between groups in this study of 70 patients and the authors concluded a larger sample size was needed. Interim analyses in this pilot will enable timely assessment of effect to inform ongoing recruitment.

An additional limitation is the ongoing impact of the COVID‐19 pandemic on elective surgery and the patient journey. When patients with cardiovascular disease requiring surgery do get an elective booking, they are frequently having to traverse the process in isolation making the capacity for self‐management more important than ever. Health services have been drastically reduced with preadmission clinics often closed or limited, the availability of telehealth variable and accompanying carers or next of kin banned. Almost 50% of cardiac rehabilitation services have ceased (Inglis et al., 2020). A resource intensive specialty, cardiac surgery is reliant on the availability of ICU beds for immediate recovery. To date, elective surgery cancellation is a common strategy employed to optimize ICU bed availability. Whilst it can be argued that nothing in cardiac surgery is truly elective, the specialty is not immune from this approach (Wynne & Smith, 2021). An additional consideration is the ongoing burden of care on critical care nurses during the pandemic that also impacts on ICU bed availability (Wynne, Conway, et al., 2021; Wynne, Davidson, et al., 2021). These factors in combination, will influence the capacity for elective surgery and as such, recruitment into the trial.

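### Eight unranked primary outcomes, and looks at intervention effect meant to inform recruitment, in a pilot sized only for the precision of one pooled readmission rate

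*Protocol article*

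**What the plan says.** The Outcome measures section sets the primary outcomes: "The primary outcome measures for this trial are representation and readmission in 30, 60, 90 days and at 12 months post surgery (reported separately". Two outcomes at four times make eight, and none is placed above the others. Under Data storage and analysis, proportions are compared between arms by chi-square or two-tailed Fisher's exact test.

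On interim work, Outcome measures states: "Ongoing interim analyses will be undertaken to assess intervention effect on representation rate that is poorly reported". Limitations gives the use of these looks: "Interim analyses in this pilot will enable timely assessment of effect to inform ongoing recruitment".

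The size is justified as follows: "assuming 15% of the population will be readmitted, a total sample size of 49 patients is required", for 95% confidence of being within 10 points. Loss to follow-up "is approximately 4% annually". Then: "The aim is to recruit 20 patients from each site to a total of 60 patients", and this number is to be reached "prior to interim analyses in this pilot study". The later trial is to be powered on 30-day readmission. Design and procedure says the pilot is needed to size that trial, while Aims and Outcome measures say it is to investigate or test effect.

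**The concern.** The article gives the pilot two tasks that its size does not support.

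The first is a test of effect on eight outcomes that all carry primary status. If any one of them reaches significance, the report can truthfully say that a primary outcome was met. The chance of that with an inert intervention is well above the level of a single test.

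The second is an early look at effect that feeds into recruitment. The sample size calculation contains no between-arm difference, so nothing shows that 60 patients can tell a useful intervention from a useless one. If the look is taken at face value, a useful programme could be dropped or a chance result pursued. Limitations offers the looks just after describing an earlier pilot on the same platform, with 70 patients, which found no advantage over usual care and whose authors wanted a larger sample. An effect look at 60 does not answer that problem.

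**Working it through.** **Inputs.** About 30 per arm: 60 patients, and "allocation ratio of 1:1 will be generated for each site". Readmission 15%: Outcome measures and Background. Representation 11.9%: the study in Background that separates the two outcomes. The 95% intervals printed there (10.5–13.7 beside 15%, 13.5–16.5 beside 11.9%) each exclude their own estimate and contain the other. The two figures may therefore be interchanged, and I show power at both rates. Two-sided 5% level: assumed, since the article states none for the arm comparison.

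**1. The plan's own figure.** n = 1.96² × 0.15 × 0.85 / 0.10² = 48.98, so 49. The stated figure reproduces. Allowing 4% loss, 49 / 0.96 = 51.04, so 52, and 60 is more than enough for that purpose. The formula describes one proportion in all patients together. For the difference between two arms of 30 at the same 15% rate, the 95% half-width is 1.96 × √(2 × 0.15 × 0.85 / 30) = 0.181, or about 18 points. That is wider than the rate itself.

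**2. False positives over eight outcomes, one analysis, no true effect.** Eight independent tests would give 1 − 0.95⁸ = 33.7%. This is an upper figure, because each outcome is cumulative over time and its four time points are correlated. I therefore use a simulation of nested binary outcomes, 30 per arm, 10,000 replicates. The cumulative rates after 30 days are assumed; ρ is the correlation between the latent variables for the two outcomes.

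| Readmission / representation at 30, 60, 90 days, 12 months | ρ | Chi-square | Fisher |
|---|---|---|---|
| 15, 20, 25, 40% / 12, 16, 20, 32% | 0 | 23.6% | 11.2% |
| same | 0.5 | 22.6% | 10.6% |
| 10, 13, 16, 25% / 8, 10, 13, 20% | 0 | 22.2% | 7.5% |
| same | 0.5 | 22.0% | 7.4% |

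A single outcome at 15% gives 5.3% (chi-square) or 1.7% (Fisher), so the excess comes from having eight.

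**3. What a look at 60 can show.** Power is the sum, over all event counts a and b, of Bin(a; 30, p₁) × Bin(b; 30, p₂) where the test gives p ≤ 0.05. The chance of no observed benefit is the same sum over b ≥ a, with b the count in the intervention arm.

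| True rates | Chi-square | Fisher | No observed benefit |
|---|---|---|---|
| Representation 11.9% v 6% | 12.7% | 3.0% | 28.1% |
| 15% v 7.5% | 15.7% | 5.3% | 23.4% |

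A true halving of representation would thus be non-significant in 87% to 97% of trials. For scale, 15% v 7.5% needs 278 per arm for 80% power (normal approximation).

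**The case against.** Several points on the other side have force.

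- **The false positive rate depends on the test.** At 30 per arm the expected events at 30 days are 30 × 0.15 = 4.5 and 30 × 0.119 = 3.6. Under the usual rule of fewer than five expected, which the article does not state, Fisher would be used there. Choosing the test by that rule gives 18% over the eight outcomes, or 16% if the two outcomes correlate strongly. A reader might infer that a false positive is probable; these figures do not support that. The rate is raised well above one test's level but stays below one in four.
- **No stopping rule is written.** A reader might infer that a non-significant look ends the study. The text says only that the looks inform recruitment, and it gives no futility criterion or threshold.
- **The number of looks is not stated.** A reader might infer an open-ended sequence of tests on all eight outcomes. Interim assessment is stated for representation only. With unadjusted looks every 60 patients, chi-square error on representation would be about 11% at three looks and 14–15% at five, but those schedules are assumptions and the point does not rest on them.
- **Recruitment may already be over.** Sixty is called the total, and at two patients a week from three sites it takes 60 / 6 = 10 weeks, within the stated 10–12. On that reading no look could halt the pilot, and the recruitment to be informed is that of the later trial. The abstract's mention of a pilot phase of a trial, together with Limitations, allows the other reading. This is an ambiguity to settle.
- **Boundaries and multiplicity methods may sit in a document not shown.** Their absence here is no finding. Which outcome is primary, and what the looks are for, are fixed in this article.
- **The different endpoints are explained.** Readmission sizes the later trial, while representation is examined because it is poorly reported. That is not a contradiction.

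It would also be wrong to judge the look by power for representation and readmission combined (27% v 13.5%: 25% by chi-square, 16% by Fisher). No interim analysis of that composite is planned.

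**Conclusion.** The point holds in a limited form and should be corrected. The article fixes eight unranked primary outcomes and gives looks at effect a role in recruitment, in a pilot whose size rests only on the precision of one pooled proportion. The any-of-eight false positive chance is about 23% (chi-square) or 11% (Fisher) at the higher assumed rates, and 22% or 7% at the lower. A look at representation has 13% or 3% power for a halving from 11.9% and shows no observed benefit about 28% of the time. The whole 60 patients are therefore a poor basis for a recruitment decision resting on effect, whether for this pilot or a later trial.

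These figures assume 30 per arm with no loss, a two-sided 5% level, and, for the false positive rate, event rates after 30 days that the article does not give. The power figures need only the 30-day rates and the size of effect. A mistaken stop remains a risk of using the look, not something the article prescribes.

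**What to change.** 1. Name 30-day readmission as the single primary outcome, since the sizing already rests on it. Make the other seven secondary, reported as estimates with 95% confidence intervals and no claim of significance.
2. Replace the between-arm interim assessment, as the basis for continuing, with recruitment per site, retention and the event rate pooled over arms. Bundle use can be added as a feasibility measure, labelled as such, because it exists only in the intervention arm and so is not arm-blind.
3. State whether recruitment ends at 60 or continues.
4. Only if pilot patients will count in a main trial: keep the results by arm closed until its end, or count this look in a group-sequential boundary. The article does not say that they will be pooled.

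All of this is wording, with no change to procedures or data collection. The loss is an early view of effect, which 60 patients could not give reliably.

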### Data storage and analysis

2.7

REDCap (Harris et al., 2009) is a secure web application used exclusively to support data capture for research studies. The intuitive interface provides concurrent data validation with entry, 256 bit encryption between the data entry client and the server, secure access, an audit trail for tracking data manipulation and export procedures, automated export procedures for data downloads to common statistical packages, data import from external sources and advanced features such as branching logic, calculated fields and data quality checks. Developed and maintained by a team at the Vanderbuilt University it is licensed free of charge by Melbourne Health (MH). The MH copy of the REDCap application and data are housed in MH secure encrypted servers. The data are securely backed up off site as per standard procedures for data security and local support is provided by MH. The study database will be created in REDCap hosted by MH. As per the approved protocol, study participants will be allocated a unique study code and identifiers entered into the study database that is configured to flag these as such in REDCap, which then provides additional protection for these data elements. Identifiers will only be available to specified individuals on the project. Identifiers will be automatically removed from all printed material generated by REDCap where the user does not have permission to access identifiers. The principal investigator (PI) will be the only member of the project team able to download data from REDCap.

The downloaded master file for statistical analyses will contain a unique Code ID so data will be reidentifiable. Data will be exported from REDCap into IBM SPSS Statistics for Windows (version 27; IBM Corp.) for analysis. Preoperative, intraoperative and perioperative data will be extracted from the ANZSCTS repository following 90‐day follow up. A minimum of 12 months after the date of surgery for the last enrolled patient, ANZSCTS data linked to the National Death Index will be accessed for the study cohort and combined with existing data that will then be screened for inconsistencies and errors. On completion of cleaning, linking variables will be removed, data will become non‐identifiable and aggregate analyses will be undertaken. Categorical data will be presented as frequency and proportion and continuous data as mean and standard deviation where normally distributed, or median with quartiles.

Preoperative demographic data, operative data and early postoperative complications will be compared between intervention and control group. Frequency of representation, readmission and mHealth metrics will be reported as proportions and the EQ5D‐5L and PAM endpoints are scale measures that will also be compared between intervention and control groups. The approach to analysis of repeated measures results from the EQ5D‐5L and PAM will be dependent on loss to follow up and normality of distribution. Categorical variables will be analysed using chi‐square (χ^2^) or two‐tailed Fisher's exact test with appropriate degrees of freedom to test for equality of proportions. Independent samples *t*‐tests (two‐tailed) will be used to test for equality of means for continuous variables or the non‐parametric equivalent Kruskal–Wallis test. Univariate factors with a *p* value ≤0.25 will be considered eligible for multivariate analysis. Multivariate logistic regression will be used to identify predictors of readmission. Direct entry techniques will be contrasted with backward stepwise selection to build a parsimonious explanatory model of association. Model sensitivity and specificity will be reviewed using receiver operating characteristic curve analysis with 95% confidence intervals calculated.

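### Section 2.7 compares the primary outcomes between arms only by tests of equal proportions, with no effect estimate and interval and no account of site; at about 30 per arm such a test says little

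*Protocol article*

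**What the plan says.** The primary outcomes are representation and readmission, reported separately at 30, 60 and 90 days and 12 months (Outcome measures, 2.6). For these, Data storage and analysis (2.7) says "Frequency of representation, readmission and mHealth metrics will be reported as proportions", and that categorical variables are compared by chi-square or by a two-tailed Fisher's "exact test with appropriate degrees of freedom to test for equality of proportions". It gives no rule for choosing between the two tests and no significance level for them.

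The only intervals planned in 2.7 belong to the prediction model: "receiver operating characteristic curve analysis with 95% confidence intervals calculated". The regression is likewise for prediction: "Multivariate logistic regression will be used to identify predictors of readmission".

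The Abstract says "permuted block randomization with an allocation ratio of 1:1 will be generated for each site". Section 2.7 does not use site in the comparison.

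The sample size in 2.6 is a precision calculation for one proportion: "assuming 15% of the population will be readmitted, a total sample size of 49 patients is required". Sixty patients are to be recruited, 20 per site. Limitations (3.1) adds: "Interim analyses in this pilot will enable timely assessment of effect to inform ongoing recruitment".

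**The concern.** The primary aim (2.1) is the effect of the intervention, and the pilot is meant to support the sample size of a full trial (2.3, 2.6) and decisions on continuing recruitment (3.1). Each of these needs an estimate of the difference between arms and a statement of its uncertainty. The sample size is itself built on estimation, but the stated analysis is a test. If that test is unlikely to reject even for a large benefit, its result barely separates a useful intervention from a useless one. A bare non-significant result could then be taken as absence of effect when the data fit anything from a large benefit to some harm.

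**Working it through.** **Inputs.** From the article: 15% readmission, total n of 49, 60 recruited, about 4% loss (2.6); 1:1 allocation within site (Abstract); almost 27% for representation and readmission combined (2.6); 32.3% readmission at 6 months in one Australian centre (Background, 1.1). Assumed: 30 per arm, two-sided 0.05, and a halving as the illustrative effect.

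**The plan's own figure.** n = 1.96² × 0.15 × 0.85 / 0.10² = 48.98, so 49. Allowing for 4% loss, 49 / 0.96 = 51.04, so 52; 60 covers it. The figure reproduces. It concerns one overall rate, not a comparison of arms.

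**What each test gives when one arm has no events.** With k events in the other arm, two-sided Fisher p = 2 × C(30,k) / C(60,k).

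- k = 4: p = 0.112
- k = 5: 2 × 142,506 / 5,461,512 = 0.052
- k = 6: p = 0.024

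Uncorrected chi-square for 0/30 v 5/30: 60 × (0 × 25 − 30 × 5)² / (30 × 30 × 5 × 55) = 5.45, p = 0.0195. With Yates' correction p = 0.062. The smallest expected count is 2.5, so the customary rule (Fisher if any expected count is below 5) would choose Fisher for this table. The article does not state that rule.

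The Fisher result is also sensitive to small losses: 0/29 v 5/28 gives p = 0.0235.

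**Rejection probability.** All outcomes of two independent binomial arms of 30 were enumerated, and the probabilities of tables with p < 0.05 summed:

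| True rates | Fisher | Uncorrected chi-square |
|---|---|---|
| 15% v 15% | 1.7% | 5.3% |
| 15% v 7.5% | 5.3% | 15.7% |
| 15% v 5% | 9.3% | 26.4% |
| 15% v 0% | 28.9% | 67.8% |
| 27% v 13.5% | 16.2% | 25.0% |
| 32.3% v 16% | 22.0% | 31.2% |

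Under the expected-count rule, power for 15% v 7.5% is 6.6%, with Fisher used in 87% of outcomes. For 80% power on that contrast, the normal approximation gives about 278 per arm.

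**What an interval would show.** Take 2/30 on intervention and 5/30 on control, unstratified, by Newcombe's method. The Wilson limits are 0.018 to 0.213 and 0.073 to 0.336. The difference is 0.067 − 0.167 = −0.100.

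- Lower limit: −0.100 − √[(0.067 − 0.018)² + (0.336 − 0.167)²] = −0.276
- Upper limit: −0.100 + √[(0.213 − 0.067)² + (0.167 − 0.073)²] = +0.074

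The estimate is −10 points, 95% CI −28 to +7. For 0/30 v 5/30 the same method gives −16.7 points (−33.6 to −2.0).

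**The case against.** A reader might infer that the planned tests cannot reach significance, so that the result is fixed in advance. The documents do not support this. Section 2.7 also allows chi-square, which without correction rejects at 0/30 v 5/30 and even at 0/30 v 4/30 (p = 0.038). Fisher rejects from 0/30 v 6/30, which gives 29% power if a 15% rate is abolished. The 15% is a 30-day readmission figure, and 2.6 expects readmission to be lowest at that point; power is higher at later or combined rates. Nor is it right that the plan yields no estimate at all: proportions are reported, and if given by arm they allow a crude difference to be derived.

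The low power comes from the sample size, not the choice of test. An interval adds no information and would often be just as inconclusive. That is true, but the interval displays the inconclusiveness and can be carried into planning; a p value does neither.

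Site adjustment and effect measures may sit in a full protocol or analysis plan that is not shown, so their absence alone would not be a finding. The point here is the method that the article does state, in a section detailed enough to describe stepwise selection and ROC analysis. Site is the lesser part. At 15%, each arm of each site (10 patients) expects 1.5 events, so combining over sites will gain little precision, and ignoring site does not invalidate the test. It simply matches the analysis to the allocation.

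Finally, the article has no rule that equates a non-significant result with no effect. Section 3.1 notes that an earlier non-significant pilot on the same platform was judged to need a larger sample. Misreading is a risk, not a stated intention.

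**Conclusion.** The point holds in this limited form: the stated between-arm method for the primary outcomes is a test of equal proportions, without an effect measure and interval and without regard to site. For a halving, power is about 5% to 16% at a 15% rate and about 16% to 31% at 27% or 32.3%. A non-significant result is likely for plausible effects and would carry little information.

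The figures assume 30 per arm, a two-sided 0.05 level and independent patients. The two higher rates are only guides: 27% combines two outcomes that the trial reports separately, and 32.3% was measured at 6 months, which is not one of the trial's time points. The change is worth making before analysis, but nothing here invalidates the pilot.

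**What to change.** In 2.7, for representation and for readmission at each time point, make the primary between-arm summary the event counts by arm and the risk difference combined over sites with Mantel-Haenszel weights, with a 95% score-type interval (for example Miettinen-Nurminen). State that no conclusion for or against effect, at an interim look or at the end of the pilot, will rest on a p value.

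The cost is analysis wording only: no new data, patients or design change. The downside is that the intervals will be visibly wide, and the change does not raise the power of the pilot.

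### No stated between-arm analysis of EQ-5D-5L and PAM uses the collected baseline or the site strata, and the repeated-measures method is left open without a rule; the cost is mainly precision

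*Protocol article*

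**What the plan says.** Section 2.7 (Data storage and analysis) says that the EQ-5D-5L and PAM "endpoints are scale measures that will also be compared between intervention and control groups". It then says that the approach to the repeated measurements of these scales "will be dependent on loss to follow up and normality of distribution". No candidate methods, threshold or decision rule follow.

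The tests it names for comparing groups are:
- for continuous variables, two-tailed independent-samples t-tests, which "will be used to test for equality of means for continuous variables", or the Kruskal–Wallis test;
- for categorical variables, chi-square or Fisher's "exact test with appropriate degrees of freedom to test for equality of proportions".

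The only regression described is logistic, and it serves to identify predictors of readmission.

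Two design features bear on this. Section 2.6 (Outcome measures) says of the two scales: "These measures will be assessed at baseline following enrolment and each time the primary outcome is assessed". Table 1 and the abstract place the follow-up scores at 30, 60 and 90 days. The abstract also says that "permuted block randomization with an allocation ratio of 1:1 will be generated for each site". The target is 20 patients at each of three sites, 60 in total, so about 30 per arm.

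**The concern.** A baseline score on the same scale is often the strongest available predictor of a follow-up score. A comparison that leaves it out carries avoidable noise, and with about 30 patients per arm that noise can be substantial. Analysing by the randomization strata likewise costs nothing once randomization has been blocked by site.

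The open choice of repeated-measures method is a separate matter. With two scales, three follow-up visits and several reasonable methods, a choice made after the data are in leaves room for selection unless the rule is fixed beforehand. Section 2.6 assigns the analysis to someone outside recruitment, allocation and outcome measurement, but the article does not say that this person is blind to arm.

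Section 2.1 makes the effect on quality of life and patient activation a stated secondary aim. Activation is also the measure closest to the self-management mechanism in the hypothesis of section 2.2. A sharper and pre-stated comparison is therefore worth having, even in a pilot.

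**Working it through.** **1. The plan's own figure.** Section 2.6 gives 49 patients to estimate a 15% readmission rate to within 10 percentage points with 95% confidence.

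n = 1.96² × 0.15 × 0.85 / 0.10² = 48.98, rounded up to 49.

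Allowing for 4% loss, 49 / 0.96 = 51.04, so 52, which is below the planned 60. The figure reproduces. It does not involve EQ-5D-5L or PAM, so nothing below alters it.

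**2. Inputs for the scales.** From the article: 30 per arm and two-tailed tests. Assumed, because the article does not give them: α = 0.05, a true difference of 0.5 SD, and a baseline-to-follow-up correlation ρ between 0.3 and 0.7.

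**3. Baseline adjustment.** It multiplies the variance of the arm difference by 1 − ρ². The effective standardized difference becomes 0.5 / √(1 − ρ²). Power comes from the two-sample t-test with 30 per arm. The single degree of freedom spent on the covariate is ignored.

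| ρ | Variance factor 1 − ρ² | Effective difference (SD) | Power | Difference detectable with 80% power (SD) |
|---|---|---|---|---|
| unadjusted | 1.00 | 0.500 | 48% | 0.74 |
| 0.3 | 0.91 | 0.524 | 51% | 0.70 |
| 0.5 | 0.75 | 0.577 | 59% | 0.64 |
| 0.7 | 0.51 | 0.700 | 76% | 0.53 |

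The last column is 0.74 × √(1 − ρ²), computed before rounding. A normal approximation gives nearly the same values: 0.72 SD unadjusted, and 0.69 to 0.52 SD adjusted.

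**4. Site, for the scales.** If site explains a share s of the variance and arms are balanced within site, the unadjusted test uses a standard error that is slightly too large. Its true type I error is 2 × [1 − Φ(1.96 / √(1 − s))]. For assumed s of 2%, 5% and 10% this is 4.8%, 4.4% and 3.9%. The test is valid and slightly conservative.

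**5. Site, for representation and readmission.** The check is the mean within-site binomial variance divided by the pooled variance at 15%, which is 0.15 × 0.85 = 0.1275. The site rates are assumed.
- Rates 8/15/22%: 0.1242 / 0.1275 = 0.974.
- Rates 5/15/25%: 0.1208 / 0.1275 = 0.948.

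That is about 3–5% of variance. With 20 patients per site, each site-by-arm cell holds about 10 patients, and at a 15% rate about 1.5 events.

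**6. Room for selection.** A null simulation used 30 per arm, baseline plus three visits, and 5,000 runs at each of ρ = 0.3, 0.5 and 0.7. A single fixed test rejected in about 5% of runs. The better of t-test and Kruskal–Wallis rejected in about 6%. The best of four analyses (t-test, Kruskal–Wallis, change-score t-test, and baseline-adjusted mean of the follow-up visits) rejected in about 12.5%. That last figure is a ceiling for free choice by p-value, which is not what the article describes.

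**The case against.** Much of this is argued from silence in a condensed article. The t-test sentence covers every continuous variable, including the demographic and operative data compared in the same paragraph, and the two scales have their own repeated-measures sentence. Covariate lists commonly sit in the statistical analysis plan, which is not shown. These are also secondary outcomes of a pilot whose size rests on a readmission rate.

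Most of that stands, and it limits the point. Three stronger readings are tempting, and the article supports none of them.

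- **That the plan excludes baseline and site.** It does not say so. It names unadjusted tests and leaves the longitudinal method open, and that method could well include the baseline visit.
- **That the comparison would be biased.** With 30 per arm, a chance baseline difference has a standard error of √(2/30) = 0.26 SD, so an imbalance of at least 0.25 SD arises in about one trial in three. Under randomization this is random error that the test's own standard error already covers.
- **That the method would be picked for its result.** The stated triggers are attrition and normality, not the treatment effect, and both can be judged without knowing the arm.

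What survives the objection is stated text. The method is expressly made to depend on observed data with no rule, and every between-arm test that is named is unadjusted.

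**Conclusion.** The point holds as a precision and pre-specification issue for two secondary outcomes. It is not an error that invalidates the trial.

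Its size depends on a correlation that the article does not give. At 0.3 the gain is modest: 9% of variance, and about 3 to 4 points of power. At 0.7 the variance is nearly halved and power at 0.5 SD reaches about 76%. Because major surgery falls between baseline and follow-up, the lower end cannot be ruled out. The 0.5 SD difference is illustrative and is not a design target of the trial.

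The site component is minor. Since blocking already balances the arms by site, it is mainly a correction to the standard error. The risk from the open choice of method is real but bounded, and stating a rule removes it.

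**What to change.** In section 2.7, state one longitudinal mixed model for each scale, with baseline score, site, visit, arm and arm-by-visit. Include all patients with any follow-up score, and report adjusted differences between arms with 95% confidence intervals at 30, 60 and 90 days. If a fallback is wanted for heavy loss to follow-up or marked non-normality, name it and its trigger in advance, and have it judged blind to arm.

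As an optional minor addition, report a site-stratified risk difference with a 95% confidence interval for representation and for readmission, noting that the gain is small and that events per site and arm are sparse.

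The cost is analysis wording only. No new data or patients are needed, the planned software can fit the model, and the target of 60 stays as it is.
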